## Abstract

**Background:**

Patients with acute brain injury often require invasive mechanical ventilation, increasing the risk of developing complications such as respiratory secretions retention. Rapid chest compression is a manual chest physiotherapy technique that aims to improve clearance of secretions in these patients. However, the rapid chest compression technique has been suggested to be associated with increased intracranial pressure in patients with acute brain injury. The aim of this work is to elucidate the effects of the technique on intracranial pressure in mechanically ventilated patients with acute brain injury. Furthermore, the effects of the technique in different volumes and flows recorded by the ventilator and the relationship between the pressure applied in the intervention group and the different variables will also be studied.

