### Intervention description {11a}

Intervention group: the application of the technique will be carried out in a single moment and will be applied with the patient in supine decubitus with 30° elevation of head and trunk, the rapid chest compression technique will be applied once in the expiratory time of each 3 respiratory cycles during 5 min by a physiotherapist. Safety monitoring of heart rate, blood pressure, intracranial pressure, peripheral oxygen saturation, and cerebral perfusion pressure will be performed by the clinical team and the principal investigator. The intervention will stop if reached some of the safety values presented below or when the clinical team considers.

Control group: the technique will be performed in a single moment and will be applied with the patient in supine decubitus with 30° elevation of head and trunk. The passive mobilization technique of the right first metatarsophalangeal joint will be applied to the available range of flexion-extension, performing 15 repetitions per minute and for 5 min by a physiotherapist. Safety monitoring of heart rate, blood pressure, intracranial pressure, peripheral oxygen saturation, and cerebral perfusion pressure will be performed by the clinical team and the principal investigator. The intervention will stop if reached some of the safety values presented below or when the clinical team considers.

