#### Applied pressure

In order to assure that the technique is performed consistently, the chest compression pressure made by the Physiotherapist will be monitored and data recorded during the procedure application time. The Tekscan ComfortMat 1 will be the device used to measure and record the pressure values (g/cm^2^).

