#### Blood O_2_ and CO_2_

Recent studies identify a tight control in the lower limits of blood CO_2_ partial pressure as a protective factor in case of brain injury, because high CO_2_ levels induce arterial vasodilatation as shown in laboratory studies. We will perform arterial blood gas 5 min prior to and at the end of the technique application.

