## Statistical methods

### Statistical methods for primary and secondary outcomes {20a}

A descriptive analysis of the collected values of the variables under study will be carried out, studying the measures of central tendency. Normal distributions will show mean and standard deviation and median and interquartile range in case of non-observation of normal distribution. The normality of the samples will be verified with the Kolmogorov-Smirnov test.

The verification of the hypothesis under study will be assessed using Student’s *T* test for independent samples in case of normality of the sample and by the *U* Mann-Whitney test otherwise.

A multiple linear regression analysis will be performed: considering as a dependent variable the intracranial pressure differences, difference or gain of expiratory flow and between the covariates, the type of technique, the pressure applied in the technique under study, the type of brain injury, blood gases changes, age, and sex.

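### The secondary regression puts technique beside applied chest pressure, which exists in one arm only, and blood-gas change, which is post-treatment, so its technique coefficient is not the total effect of the technique

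*Protocol article*

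**What the plan says.** Section {20a} of the protocol article describes two inferential analyses.

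- The main hypothesis is tested without covariates: "The verification of the hypothesis under study will be assessed using Student’s" t test if the data are normal, and the Mann-Whitney test otherwise.
- A multiple linear regression follows, "considering as a dependent variable the intracranial pressure differences, difference or gain of expiratory flow", with these among the covariates: "the type of technique, the pressure applied in the technique under study, the type of brain injury, blood gases changes, age, and sex".

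Other sections show what two of those covariates are.

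- **Applied pressure.** The section of that name states that "the chest compression pressure made by the Physiotherapist will be monitored and data recorded during the procedure application time". The abstract ties it to one arm: "the relationship between the pressure applied in the intervention group and the different variables will also be studied". Under {11a} the controls receive a toe procedure: "The passive mobilization technique of the right first metatarsophalangeal joint will be applied to the available range of flexion-extension".
- **Blood gases.** The section on blood O2 and CO2 sets the timing: "We will perform arterial blood gas 5 min prior to and at the end of the technique application". It also states that "high CO_2_ levels induce arterial vasodilatation".

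The secondary objectives ask how ICP relates to injury type and to peak expiratory flow, and how applied pressure relates to the other dependent variables.

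**The concern.** A technique coefficient in a two-arm trial estimates the total effect of allocation only if the other terms in the model are not themselves products of allocation. Two of the listed terms are. Applied pressure is part of the compression procedure and has no counterpart in the control arm. Blood-gas change is partly measured at the end of the procedure, so the technique can cause it, and the article itself supplies a mechanism by which CO2 could act on ICP.

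The trial asks whether the technique is safe. A technique coefficient that is inestimable, very imprecise, or cleared of one pathway could be misread as showing no independent effect on ICP. The same listing also weakens the pressure objective: holding gas change fixed can take out part of any relation between pressure and ICP.

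**Working it through.** **Inputs from the article.** 25 patients per arm (Sample size {14}) and an equivalence limit of 2.0 mmHg. The article gives no figure for the regression and no distribution for pressure or blood gases. The 25 per arm reproduces with SD 2.5 mmHg, two-sided alpha 0.05 and 80% power: 2 × (1.960 + 0.842)² × 2.5² / 2.0² = 24.5, rounded up to 25. The sample size is not in dispute; it only supplies n below.

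**Step 1: control pressure left missing.** Complete-case fitting keeps only the compression arm. Technique is then constant and has no estimable coefficient.

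**Step 2: control pressure coded as raw zero.** Take technique T (0/1) and pressure P, with mean m and SD = CV × m in the compression arm. The slope c on P comes from the compression arm alone, and the technique coefficient is

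b = (mean ICP difference, compression − c × m) − (mean ICP difference, control).

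This is the contrast for a compression of zero pressure, which no patient receives. With residual variance s²:

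- with P: Var(b) = s² × [1/25 + 1/25 + 1/(24 × CV²)]
- without P: Var(b) = s² × 2/25 = 0.08 s²

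| Assumed CV | 1/(24 × CV²) | Variance ratio | SE ratio |
|---|---|---|---|
| 10% | 4.167 | 4.247/0.08 = 53.1 | 7.29 |
| 20% | 1.042 | 1.122/0.08 = 14.0 | 3.74 |
| 30% | 0.463 | 0.543/0.08 = 6.8 | 2.61 |

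The more uniform the pressure, the larger the ratio, and uniform application is the stated reason for recording pressure.

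**Step 3: pressure centred on the compression-arm mean, controls set to 0 on that scale.** Now m = 0 in the formula for b. In this two-variable model b is the plain difference in arm means, and the extra variance term vanishes. Subtracting one constant from all 50 values does not achieve this, because b does not change when P is shifted for everyone.

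**Step 4: adjusting for blood-gas change.** Total effect = effect not through CO2 + (ICP slope on CO2 × CO2 change caused by the technique). Adjustment removes the second term. With an assumed slope of 0.5 mmHg per mmHg:

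- CO2 rises by 2 mmHg: the CO2 part is +1.0. A total of 2.0 becomes 1.0 after adjustment.
- CO2 falls by 2 mmHg: the CO2 part is −1.0. A direct effect of 1.0 gives a total of 0, and adjustment raises the estimate from 0 to 1.0.

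The article fixes neither the slope, nor the change, nor its sign.

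**Step 5: simulation.** 4,000 runs, 25 per arm, residual SD 2.0, assumed true total effect 2.0 mmHg, raw-zero coding, CV 25%. Entries are the mean technique coefficient, with its empirical SE in brackets.

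| Assumed pathway | Neither covariate | Adjusted |
|---|---|---|
| All proportional to pressure | 2.00 (0.58) | −0.02 (1.79), for pressure |
| Half proportional to pressure | 1.99 (0.56) | 1.00 (1.81), for pressure |
| Half through a CO2 rise | 2.02 (0.63) | 1.01 (0.64), for gas change |
| Half through each | 1.99 (0.63) | 0.01 (1.82), for both |
| Neither related to ICP | 2.00 (0.57) | 2.00 (1.79), for both |

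The last row has no bias, only lost precision. Without the two covariates, the total effect is recovered in every row.

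**The case against.** **The main inference is untouched.** A reader might infer that the trial's conclusion on ICP is invalid. The article does not support that. The main hypothesis rests on an unadjusted t test or Mann-Whitney test that neither covariate enters, and nothing says the regression coefficient will be reported as the treatment effect. This stands, and it limits the point to a secondary analysis.

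**The list may be a pool of candidates.** The sentence names more than one dependent variable, the abstract already frames the pressure question within the intervention group, and an unseen analysis plan may settle models and coding. This stands in part: a single joint model is one reading. But the article does list these covariates together for one regression, and any plan that separated them would have to depart from that wording.

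**The standard-error inflation depends on coding.** This stands. Missing and raw zero are not the only options, and step 3 removes the inflation. The CVs are also assumed.

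**The CO2 effect could go either way.** This stands. It is tempting to say that adjustment would hide a harmful rise in ICP, but if compression lowers CO2, adjustment would enlarge the estimated rise. The authors may also want a CO2-independent effect, since their discussion aims to control as many interactions as possible. That is a legitimate question, but a different one from the total effect, and it needs its own label.

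**Baseline ICP.** A reader might count its absence from the covariates as a further error. The outcome is already an ICP difference, so adding it is a gain in precision, not a correction.

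**Conclusion.** The point holds for the secondary regression. Two facts carry it, and both are in the article: compression pressure is defined in one arm only, and blood-gas change is measured after treatment, with a stated vascular action of CO2. Read as one model, the technique coefficient is inestimable (control pressure missing), an extrapolation to zero pressure (raw zero), or a contrast with any CO2-mediated part removed.

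The size is illustrative. The 7.3, 3.7 and 2.6-fold standard-error ratios hold for raw-zero coding at assumed CVs of 10%, 20% and 30%, and they disappear with centring within the arm. Centring does not cure the adjustment for gas change, whose size and direction the article leaves unknown. The main hypothesis test is not affected, and its validity does not depend on the correction.

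**What to change.** Amend the regression paragraph in {20a}.

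1. **Between-arm model:** regress the ICP difference on technique with pre-treatment covariates only: injury type, age, sex and, for precision, pre-intervention ICP. Treat the expiratory-flow outcome likewise, without applied pressure or gas change.
2. **Pressure:** analyse it in a separate dose-response model within the compression arm. Those 25 patients are the only ones who can inform this secondary objective. Leave gas change out of the main version of this model as well.
3. **Blood-gas change:** analyse it as an outcome, or in a mediation analysis labelled exploratory.
4. **Data release:** {17a} says analysts are blinded, and a compression-pressure column reveals the arm. Release it only after the primary analysis is locked.

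The cost is a change of wording and a little more analysis work. No new patients, measurements or visits are needed, and the pressure objective is still answered.

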### Interim analyses {21b}

## Oversight and monitoring

### Composition of the data monitoring committee, its role and reporting structure {21a}

DMC will not be needed due to the clinical nature of all the data.

### Plans for communicating important protocol amendments to relevant parties (e.g., trial participants, ethical committees) {25}

Protocol changes will be communicated to the Ethics Committee of Galicia and data updated at the Clinical Trials page.

### Dissemination plans {31a}

The study results and conclusions are intended to be published in 1st quartile physical therapy journals or intensive care journals.

As this is a clinical issue that should be known because it’s relevant to patients and professionals, we intend to publish it in international journals of intensive care and physiotherapy (Tables 1 and 2).

**Table 1 Tab1:** Intensive care journals - 2018 Journal Impact Factor, Journal Citation Reports Science Edition (Clarivate Analytics, 2018)

Intensive care	
*American Journal of Respiratory and Critical Care Medicine*	IF: 16,494 1st Q
*Chest*	IF: 9,657 1st Q
*Intensive Care Medicine*	IF: 18,967 1st

**Table 2 Tab2:** Physiotherapy journals - 2018 Journal Impact Factor, Journal Citation Reports Science Edition (Clarivate Analytics, 2018)

Physiotherapy	
*Neurorehabilitation and Neural Repair*	IF: 3,757 1st Q
*Journal of Physiotherapy*	IF: 5,551 1st Q
*Physical Therapy*	IF: 3,043 1st Q

## Discussion

Nowadays, the chest physiotherapy techniques are applied with several restrictions because of their effect in the intracranial pressure values, at least as referred to in several publications [5–12].

The main problem that we observe in almost every publication about the chest physiotherapy techniques in acute cerebral injured patients is that they usually include a protocol that has secretion suction at the end without separation of the effects. It’s known that the suction has clear reflex effects that increase the ICP and MAP even when patients are sedated, as shown in a recent study from Singh et al. (2018) [12] where they studied different drug effects on intracranial pressure, applying chest percussion and suctioning.

We believe, for our clinical experience and some publications that when adequately applied, rapid chest compression is safe and patients can benefit from its use, because invasive mechanical ventilation increases the risk of respiratory complications, making the management of acute cerebral injuries more complex and its influence is unknown on the outcomes [1–5, 10, 12].

In our trial, we intend to control the larger number of possible interactions to avoid results that can be affected by collateral techniques.

### Trial status

We will start the recruitment in January 2021, and we expect to end approximately in 1 year, because of the COVID-19 impact.

## Abbreviations

IMV: Invasive mechanical ventilation
MAP: Mean arterial pressure
PEEP: Positive end-expiratory pressure
FiO_2_: Inspired oxygen fraction
RASS: Richmond agitation and sedation scale
CT scan: Computerized tomography scan
MTTPh: Metatarsophalangeal
ICP: Intracranial pressure
HR: Heart rate
CPP: Cerebral perfusion pressure
PI: Principal investigator
DMC: Data Management Committee
IF: Impact factor
Q: Quartile
